## Abstract

**Introduction:**

The scale-up of antiretroviral therapy (ART) across sub-Saharan Africa (SSA) has reduced mortality so that increasing numbers of children with HIV (CWH) are surviving to adolescence. However, they experience a range of morbidities due to chronic HIV infection and its treatment. Impaired linear growth (stunting) is a common manifestation, affecting up to 50% of children. However, the effect of HIV on bone and muscle development during adolescent growth is not well characterised. Given the close link between pubertal timing and musculoskeletal development, any impairments in adolescence are likely to impact on future adult musculoskeletal health. We hypothesise that bone and muscle mass accrual in CWH is reduced, putting them at risk of reduced bone mineral density (BMD) and muscle function and increasing fracture risk. This study aims to determine the impact of HIV on BMD and muscle function in peripubertal children on ART in Zimbabwe.

**Methods and analysis:**

Children with (n=300) and without HIV (n=300), aged 8–16 years, established on ART, will be recruited into a frequency-matched prospective cohort study and compared. Musculoskeletal assessments including dual-energy X-ray absorptiometry, peripheral quantitative computed tomography, grip strength and standing long jump will be conducted at baseline and after 1 year. Linear regression will be used to estimate mean size-adjusted bone density and Z-scores by HIV status (ie, total-body less-head bone mineral content for lean mass adjusted for height and lumbar spine bone mineral apparent density. The prevalence of low size-adjusted BMD (ie, Z-scores <−2) will also be determined.

**Ethics and dissemination:**

Ethical approval for this study has been granted by the Medical Research Council of Zimbabwe and the London School of Hygiene and Tropical Medicine Ethics Committee. Baseline and longitudinal analyses will be published in peer-reviewed journals and disseminated to research communities.

Strengths and limitations of this studyThis study will provide novel understanding of the effects of HIV on bone and muscle development in a large population of sub-Saharan African children living with HIV by using ‘gold standard’ size adjustment methods for dual-energy X-ray absorptiometry (DXA), which are crucial for assessing a population with inherent size differences.Bone architecture measurement using peripheral quantitative computed tomography (pQCT) will provide understanding of trabecular and cortical bone geometry and strength in children with HIV (CWH).This study will generate new data for total body and lumbar spine DXA, tibial pQCT, hand grip strength and standing long jump for Zimbabwean children without HIV which will inform normative reference data.While the age range in this study, 8–16 years, will allow analysis of pubertal delay in CWH, the follow-up period is insufficient to determine the impact on attainment of peak bone mass which probably occurs in the early 20s.

## Introduction

Sub-Saharan Africa (SSA) disproportionally bears the burden of global HIV infection, with nearly 90% of the estimated 2.1 million children under 15 years of age living in SSA.^1^ The global scale-up of antiretroviral therapy (ART) has dramatically improved survival of children with HIV (CWH).^2^ However, there is accumulating evidence that the growing number of these children are now reaching adolescence in SSA with multisystem chronic comorbidities associated with HIV infection and/or its treatment.^3^

Poor linear growth (ie, stunting) is one of the most common manifestations of perinatally (vertically) acquired HIV infection, affecting up to 50% of children.^4 5^ Linear growth is greatest in adolescence during the pubertal development period. Bone mass is thought to change throughout the life course and may be altered by HIV^6 7^ (figure 1). The majority of peak bone mass (PBM), the maximum amount of bone accrued by the end of skeletal maturation, is attained during adolescent growth; by age 18 years in women and age 20 years in men, 80% of PBM is attained.^8^ After PBM is reached, there is no net gain in bone mass. Therefore, PBM is the net reservoir of bone for later life, a key determinant of adult bone mineral density (BMD) and consequently of adult osteoporotic fracture risk.^9^ Linear growth is therefore intimately linked to skeletal development but how HIV infection affects bone development in peripubertal SSA children is largely unknown. The prevalence of low BMD has been found to be higher in CWH than uninfected children in high-income and middle-income countries (7% in the USA,^10^ 32% in Brazil^11^ and 24% in Thailand^12^) compared with 1% in children without HIV in the USA.^10^ No study has estimated the prevalence of low BMD in SSA, and the prevalence of and risk factors for low BMD in African CWH are not known.^6 13^ It is important to highlight that the risk of poor bone accrual, reflected in low BMD measurements, is likely to be different in low-income countries compared with high-income countries due to factors such as malnutrition and social deprivation, but critically due to delayed ART initiation. A recent meta-analysis has shown that the median age of ART initiation in North America is 1 year, compared with 8 years in SSA.^14^

**Figure 1 F1:**
[figure not shown]
Hypothesised changes in bone mass across the life course in HIV-infected and HIV-uninfected individuals.

The mechanisms by which HIV may lead to low size-adjusted BMD in children are not fully understood but are likely multifactorial, including HIV-associated factors (eg, ART drugs, HIV disease stage) and traditional risk factors (eg, hypogonadism, smoking, alcohol, low physical activity and vitamin D deficiency).^15^ HIV infection promotes systemic immune activation and production of inflammatory cytokines (eg, tumour necrosis factor α), which, in turn, promote increased bone resorption.^16^ ART initiation, particularly with tenofovir (part of the first-line ART regimen in SSA), predicts an initial decline in BMD which stabilises after 2 years in adults.^17^ It is thought that tenofovir may cause renal proximal tubule toxicity, resulting in phosphate wasting and increased bone turnover.^18^ Although tenofovir and protease inhibitors have been associated with low BMD in adults,^19 20^ studies in children have shown inconsistent findings.^21–23^ Malnutrition, opportunistic infections and social deprivation may also impede musculoskeletal development. Reduced physical activity, associated with HIV,^24^ may also impair muscle development and limit impact loading to reduce osteocyte-mediated bone accrual.^25 26^ In adults, weak grip strength has been associated with increased falls and fracture risk.^27^ Although muscle (lean) mass has also been shown to predict the magnitude of bone accrual during growth,^28^ few studies have compared muscle strength and function between children with and without HIV. Interestingly, a small Canadian study showed deficits in muscle power in CWH.^29^

Another mechanism by which HIV may exert effects on BMD is through its effect on puberty. Even in the presence of ART, the onset of puberty is delayed by approximately a year in CWH in both high-income^30^ and low-income settings.^31^ Older age at ART initiation has been shown to be a significant risk factor for pubertal delay in Zimbabwean CWH.^31^ Pubertal delay in HIV may be mediated through nutritional deficiency, recurrent infection or chronic immune activation disrupting hormonal regulation.^31^ Delayed puberty may be advantageous for linear growth; spending more time in puberty may allow more time for skeletal growth.^31^ Conversely, delayed puberty has been shown in studies in high-income settings to be detrimental to bone mass accrual.^32 33^ However, the impact of pubertal delay on BMD in low-income countries remains unknown. Pubertal delay can be assessed objectively using hand radiographs. Analysis of the growth plate development and fusion of long bones in the hands can accurately quantify bone age, which is a measure of skeletal maturation. Bone age lagging behind chronological age reflects pubertal delay.^34^

BMD is commonly measured by dual-energy X-ray absorptiometry (DXA) as two-dimensional (areal) BMD; however, this is highly dependent on bone size.^35^ DXA underestimates areal bone density in short children, with smaller bones, and overestimates BMD in taller children, with bigger bones, despite the fact that they may have identical volumetric BMD. Size adjustment of DXA measures is therefore critically important in children with chronic diseases such as HIV, where smaller size due to poorer growth and delayed puberty may explain findings of lower BMD. The two ‘gold standard’ size-adjustment techniques chosen from the International Society for Clinical Densitometry are as follows: bone mineral apparent density at the lumbar spine (LS BMAD) and regression based total-body less-head (TBLH) bone mineral content (BMC) for lean mass adjusted for height (TBLH BMC^LBM^)^36^ Z-scores. As there are currently no published reference DXA data for child or adolescent populations in SSA, in this study we will use the best available data sets from high-income countries such as the UK^36^ to generate Z-scores.

Unlike DXA, peripheral quantitative computed tomography (pQCT) takes into account bone size by directly measuring volumetric BMD. It has the additional advantage of separately assessing trabecular and cortical bone compartments, providing information on bone architecture. Furthermore, a range of bone strength indices, for example, strength stain index, validated against fracture risk can be calculated.^37 38^ In high-income countries, markedly abnormal trabecular and cortical architecture have been shown in adults with HIV,^39^ and abnormal bone architecture and impaired bone strength through to early adulthood have been shown in boys with HIV infection.^39^ Few studies have assessed bone architecture and strength in CWH in SSA.

The IMVASK (IMpact of Vertical HIV infection on child and Adolescent Skeletal development in Harare, Zimbabwe) study aims to determine the prevalence of low size-adjusted BMD and muscle function (grip strength and standing long jump) in Zimbabwean children with and without HIV. pQCT assessment will enable understanding of the impact of HIV infection on bone architecture and strength. This study will further contribute to local reference data for DXA measures, bone age and muscle function (grip strength and standing long jump) for an SSA population, establishing a biorepository for future research. Study results will aid understanding of bone and muscle accrual in the context of HIV infection in the era of ART.

## Methods and analysis

### Study objectives

This study aims to determine the impact of HIV infection on size-adjusted bone density in peripubertal children aged 8–16 years established on ART. In addition, this prospective study aims:

To quantify the prevalence of low size-adjusted BMD and low muscle function (grip strength and standing long jump) among CWH compared with uninfected children.To investigate the risk factors for low size-adjusted bone density and low muscle function (grip strength and standing long jump) among CHW.To compare the rates of bone mass accrual over 1 year between children with and without HIV and assess for interaction by pubertal stage to determine if CWH exhibit catch up growth.To determine the differences in bone architecture measured by pQCT between children with and without HIV.

### Study hypothesis

We hypothesise that HIV infection adversely affects skeletal development, such that CWH, despite ART, accrue less bone mass and strength and have reduced muscle function during skeletal development.

### Study design

CWH aged 8–16 years and established on ART (n=300) and a comparison group of children without HIV, frequency-matched for age and sex (n=300) will be recruited into a prospective cohort study. Detailed musculoskeletal assessments will be conducted at baseline and after 1 year.

### Study setting

Parirenyatwa and Harare Hospital are the largest public-sector referral hospitals in Harare.^40 41^ The paediatric HIV clinics at both hospitals provide HIV care to more than 2000 children. Although HIV care is increasingly decentralised to primary care level across the country, most children in Harare continue to receive care within HIV clinics in secondary healthcare facilities. Parirenyatwa hospital has a well-functioning radiology department which houses the University of Zimbabwe DXA and pQCT research unit and has access to private radiology services in the surrounding area. The hospital catchment areas have over 116 primary and 42 secondary government schools with an estimated 157 962 children enrolled.^42^ School attendance in Harare province is high and does not differ by HIV status, with 96% of children under 18 years attending school.^43^

### Recruitment of participants

#### Eligibility

Inclusion criteria: age 8–16 years (includes prepubertal and peripubertal children), living in Harare, and in CWH only if:

Taking ART for at least 2 years (as adult studies demonstrate ART initiation is followed by an initial decline in BMD which stabilises after 2 years).^17^
The child is aware of their HIV status, to avoid inadvertent disclosure as a result of study participation.

Children with perinatally acquired HIV will be included in this study. Perinatally acquired HIV will be defined based on Zimbabwean criteria, that is, self-report of no sexual debut or blood transfusions, a history of natural sibling or maternal HIV and characteristic clinical features of longstanding HIV. Children with horizontal infection will also be included in the study.

Exclusion criteria: acute illness (requiring immediate hospitalisation) and lack of consent.

Detailed information on all the above comorbidities will be collected using the main study questionnaire in the clinical history section. This information will be collected for both children with and without HIV. Comorbidities will not be used as the basis of excluding children from the study. However, for the purposes of deriving normative DXA data, those with severe bone disease will be excluded at the analysis stage.

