Baseline mean TBLH BMC^LBM^ and LS BMAD Z-scores and the prevalence of low TBLH BMC^LBM^ and LS BMAD Z-score will be compared between CWH and without HIV. Among CWH, the association between a priori defined risk factors (ART duration, ART type, proportion of life on treatment, age at ART initiation, CD4 count, viral load, bone age, pubertal stage, nutrition, socioeconomic status and orphanhood) against size-adjusted BMD will be examined using multivariable linear regression (Z-score as a continuous variable) and multivariable logistic regression (as defined by the Z-score cut-off of <−2). Successful antiretroviral therapy will be defined as a viral load of less than 1000 copies/mL. Paired sample t-test or non-parametric Wilcoxon test will be used to assess for differences in TBLH BMC and LS BMAD on children with and without HIV between baseline and follow-up. Multivariable linear regression will be used to analyse the mean percentage change in TBLH BMC^LBM^ (g) and LS BMAD (g/cm^3^) between children with and without HIV. Models will be adjusted for physical activity, calcium and vitamin D intake. Interaction between the effects of pubertal stage (bone age) and HIV on change in TBLH BMC^LBM^ and LS BMAD will be investigated to see if differences in bone density become more or less pronounced through puberty, that is, whether catch-up growth is possible, see figure 2. The regression coefficient (β) for percentage change in size-adjusted bone mass may suggest either no growth impairment (figure 2A), delayed puberty while maintaining the same growth trajectory (figure 2B) or delayed puberty with a reduced growth trajectory (figure 2C) in CWH. If β is markedly more positive in CWH, this suggests that catch-up growth may be possible (figure 2D). Pubertal delay in this study will be defined as the lack of the initial signs of puberty (Tanner stage 2) at an age that is more than 2 SD beyond the population mean^51^ and as chronological age minus bone age >2 years.^52^ Data for total body and lumbar spine DXA, tibial pQCT, hand grip strength and standing long jump in CWH will be analysed with reference to the comparator group of children without HIV.

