## Discussion

Although the scale-up of prevention of mother-to-child transmission has reduced perinatal HIV transmission, coverage is still not universal in most parts of SSA and therefore perinatal HIV infection is expected to affect large numbers of children for years to come. Furthermore, the scale-up of ART has reduced HIV-associated mortality dramatically so that CWH, who would previously have died in infancy or early childhood, are now reaching adolescence in increasing numbers. It is therefore important to understand the impact of HIV infection and its treatment on skeletal development during the critical period of puberty.

This study will determine the prevalence of low size-adjusted BMD in children with and without HIV in Zimbabwe, a country with a severe sustained early onset HIV epidemic. In addition, this study will determine risk factors for low size-adjusted BMD in CWH. We aim to identify factors amenable to intervention, which may be modifiable to maximise future bone health and minimise subsequent adult osteoporotic fracture risk. For example, reduced muscle function predicting low size-adjusted BMD may suggest targeted physiotherapy would be of benefit, which would warrant formal investigation.

Our study will provide insights regarding the mechanisms through which perinatal HIV infection affects the timing of pubertal onset and bone mass accrual. By measuring bone and muscle parameters at baseline and 1 year and by employing ‘gold standard’ size-adjustment methodology for DXA-measured BMD in the growing skeleton, this study will also provide insights into whether catch-up growth in terms of bone mass accrual is possible in HIV despite pubertal delay and provide age-related growth velocity data for CWH, with and without puberty.

While the age range in this study will allow analysis of pubertal delay in CWH, the follow-up period is insufficient to determine the impact on attainment of PBM, which probably occurs in the early 20s.^8^ In addition, this study is not sufficiently powered to analyse the effect of individual ART types on size-adjusted bone density. An additional limitation is the inability to obtain accurate height data for CWH prior to enrolment to fully study growth recovery. This is problematic given the significant role of poverty and nutrition, independent of HIV status, in the first 1000 days of childhood^53^; this may explain some of the deficit in final height attained by CWH.

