The bone architecture measured by pQCT in this study will provide separate assessments of trabecular and cortical bone density, and bone geometry and strength in Zimbabwean children. The evidence from studies in adult men established on ART demonstrates impairments in trabecular and cortical bone architecture.^54^ Whether the same applies to children needs to be determined.

Furthermore, we will establish novel comparator data for DXA, pQCT, bone age, hand grip strength and standing long jump for a Zimbabwean population, which will be used for future research in this context. Although this represents the first steps towards developing normative reference data, the extent to which the children without HIV infection in this study are representative of the Zimbabwean population of 8–16 year olds is unknown. Furthermore, this study will establish a biorepository for future research, for example, potential bone turnover marker measurement and genotyping.

Given the magnitude of the HIV epidemic in SSA and the large cohort of young people who may experience impaired bone accrual, musculoskeletal disability or fracture as they reach adolescence and early adulthood, it is imperative to characterise the impact of perinatal HIV on musculoskeletal development.

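### The ART-timing risk-factor models mix perinatally and horizontally infected children, so HIV-free years count as time before treatment and the slopes may be understated

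*Protocol article*

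**What the plan says.** **Who is enrolled.** Eligibility gives a rule for perinatal infection: "Perinatally acquired HIV will be defined based on Zimbabwean criteria, that is, self-report of no sexual debut or blood transfusions", together with a family history of HIV and clinical signs of long-standing disease. It then adds: "Children with horizontal infection will also be included in the study". No cap or quota by route of infection is set. The quotas under Recruitment of children with HIV are by age and sex only.

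**What is analysed.** Statistical analysis compares children with and without HIV as two groups. Among those with HIV, it relates size-adjusted bone density to a list of risk factors fixed in advance, which includes ART duration and "proportion of life on treatment, age at ART initiation". Route of infection and time since infection are not on the list, and the perinatal definition is given no analytic role.

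**What is to be concluded.** The formal aim is general: "This study aims to determine the impact of HIV infection on size-adjusted bone density in peripubertal children aged 8–16 years established on ART". The study name is narrower: "IMpact of Vertical HIV infection on child and Adolescent Skeletal development in Harare, Zimbabwe". So is the Discussion: "Our study will provide insights regarding the mechanisms through which perinatal HIV infection affects the timing of pubertal onset and bone mass accrual".

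**The concern.** Age at starting ART and share of life on treatment measure exposure to untreated HIV only if infection dates from birth. The article's reasoning relies on that meaning. The Introduction treats delayed ART as critical to poor bone accrual and names older age at starting as a risk factor for pubertal delay.

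In a horizontally infected child, the years before ART are mostly years without HIV. The two variables then give the same value to two different histories, and no variable on the list separates them. What is at stake is the risk-factor objective: a real effect of late treatment could be reported as weak or absent. A second, smaller matter is that perinatal conclusions are promised from a group that is not wholly perinatal.

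**Working it through.** The article gives no figure for the number of horizontally infected children or for their bone deficit, so there is no stated figure to reproduce. Everything below on size rests on labelled assumptions.

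**1. The coding, by example.** Two 16-year-olds both start ART at 14.
- Child A, infected at birth: share of life treated (16 − 14)/16 = 12.5%; untreated years with HIV = 14.
- Child B, infected at 13: share of life treated 12.5%; untreated years with HIV = 14 − 13 = 1.

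Age at start, ART duration and share of life treated are identical. Untreated exposure differs by 13 years.

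**2. Effect on the slope, by hand.** Suppose the deficit is linear in untreated years. Let f be the horizontal share, D the distance of these children's start age from the perinatal mean at the same age, G the coded minus the true untreated years, and σ the SD of perinatal start age given age. Ignoring the small shift in the age coefficient,

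lost fraction of slope = f·D·G / (σ² + f·D²).

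Inputs:
- Age 15.5, the middle of the 14–16.99 band (Recruitment of children with HIV).
- Start 3 years before enrolment, so 12.5 (assumed; Eligibility requires at least 2 years of ART).
- Perinatal mean start 8 years, borrowed from the regional median in the Introduction. So D = 12.5 − 8 = 4.5.
- G = 12.5 − 1 = 11.5 with one untreated year, or 12.5/2 = 6.25 if the coded years do half the harm.
- σ = 2 or 3 years (assumed).

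| f | σ | G = 11.5 | G = 6.25 |
|---|---|---|---|
| 2% | 2 | 1.035/4.405 = 23% | 0.5625/4.405 = 13% |
| 2% | 3 | 1.035/9.405 = 11% | 0.5625/9.405 = 6% |
| 5% | 2 | 2.5875/5.0125 = 52% | 1.40625/5.0125 = 28% |
| 5% | 3 | 2.5875/10.0125 = 26% | 1.40625/10.0125 = 14% |

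**3. Effect on the slope, by simulation.** The set-up was 300 children on the article's age quotas, all with at least 2 years of ART, and the model adjusted for age. Horizontal infections were placed in the oldest band, with ART started 2–4 years before enrolment. Their true exposure was one untreated year or half the coded years. With three assumed perinatal start-age distributions, the fraction of the true slope recovered was 74–91% at a 2% share (6 children) and 52–82% at 5% (15 children). Another choice of distributions gave 77–91% and 55–80%. A recheck with four (uniform up to 2 years before enrolment; skewed early; normal with SD 3 centred at 5 or at 8 years, truncated) gave 69–93% and 43–85%. Attenuation of about 10–25% and 20–45% is therefore a fair middle, not a bound.

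**4. The primary comparison, for contrast.** If horizontally infected children have r times the perinatal effect, the pooled difference is δ(1 − f + f·r). Take δ = 0.23 Z from Sample size, purely as a scale:
- f = 5%: 0.23 × 0.95 = 0.2185 (r = 0), or 0.23 × 0.975 = 0.224 (r = 0.5).
- f = 2%: 0.23 × 0.98 = 0.2254 (r = 0).

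The pooled mean changes at most in proportion to the share. The slope changes several times more, because these children lie at the late-start end.

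**The case against.** **The aim is HIV in general.** Study objectives, Study hypothesis and Outcome measures all speak of HIV infection or HIV status, and Eligibility admits both routes openly. This stands. A reader might infer that pooling dilutes or biases the primary result. The article does not support that, because the pooled contrast is what it sets out to estimate. The small reductions in step 4 count as dilution only if the target is perinatal HIV and the effect in the other children is smaller, and the article states neither for its primary outcome.

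**The variables are literally correct.** Age at starting ART is the right number for every child, and the article never defines it as years of untreated HIV. It would therefore be wrong to say that the plan miscodes the data. The difficulty is interpretation: the Introduction gives the variable a meaning that holds only for infection from birth. Table 1 also collects age at diagnosis, WHO stage and lowest CD4 count, but these are not on the risk-factor list. Age at diagnosis does not separate late infection from late diagnosis either.

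**The share may be very small.** A horizontally infected child must have been infected, treated for at least 2 years and told of the diagnosis, all before age 17. In the youngest band, ART must have begun before about age 9. This limits the share, and is why 2% and 5% are used here. A 15% share confined to the oldest band would mean 45 of its 100 children, which nothing in the article supports.

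**An analysis plan may cover it.** A perinatal-only sensitivity analysis could sit in a document not shown, and its absence from an article is no fault. The point concerns what the article does state: a mixed population, a listed set of timing variables, and a perinatal conclusion.

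**Restriction may select.** The perinatal definition uses clinical signs of long-standing HIV, and the Introduction calls stunting one of the commonest manifestations of perinatal infection. Restricting could favour sicker children. This stands and shapes the fix.

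**Conclusion.** The concern holds for the ART-timing risk-factor models. As described, they include children for whom time before ART is largely time without HIV, with nothing on the list to tell them apart. Attenuation follows if HIV-free years harm bone less than untreated HIV does. Its size rests on an unstated share and on an assumed linear deficit with late-starting horizontal infections: about 10–25% at 2% and 20–45% at 5%. If no horizontally infected children are enrolled, the problem vanishes.

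For the primary comparison the conclusion is narrower. The pooled analysis agrees with the formal aim and need not be replaced. By itself it does not support the Discussion's promised insight into "mechanisms through which perinatal HIV infection affects the timing of pubertal onset and bone mass accrual". The closing remark that "it is imperative to characterise the impact of perinatal HIV on musculoskeletal development" is rationale rather than a promised result, and adds little.

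**What to change.** 1. Use the Eligibility definition to classify each child with HIV by route of infection, and report the numbers.
2. Fit the models for age at starting ART, share of life on treatment and ART duration in perinatally infected children. Show the all-children fit as a sensitivity analysis.
3. Keep the pooled primary comparison, report a perinatal-only comparison beside it, and rest statements about perinatal or vertical HIV on the latter.

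**Cost.** No extra visit is needed and the classification rule is already written. Intervals widen slightly. For the perinatal-only comparison, leaving out 5% of the HIV group without replacement takes power for a 0.23 Z difference from 80.4% to 79.4%. That uses an SD of 1.0, the value at which 0.23 corresponds to 80% power with 300 per group. At the stated SD of 1.3, the two-sided detectable difference is (1.960 + 0.842) × 1.3 × √(2/300) = 0.297, which is a separate matter. The other cost is possible selection on severity through the definition, which is why both fits should be shown.
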